# data collected and evaluation criteria

## data collection

Information relating to each patient will be noted in the observation notebook, using a black ballpoint pen, during the course of the study. Each page of the observation notebook will be dated and initialled or signed by the investigator. The investigator may delegate completion of this notebook to another authorised person, provided that he or she checks and initials the entries. The people authorised to complete the observation notebook are those members of the CMJK listed above in the practical information section.

## functional and clinical data

The following will be carried out at each consultation (C0, Ci and Cf):

- General physical examination, with measurement of height, weight and cranial circumference (CC);
- Neurological examination, including the systematic examination of abnormal movements, nystagmus, protrusion of the tongue, tremors, tonus, static position, walking, osteotendinous reflexes and sphincter control;
- The revised Brunet-Lezine test, assessing developmental age (DA) [[[14]](#endnote-14)]. Photocopies of the results will be rendered anonymous and included in the observation notebook.
- Collection of information about associated treatments.

The following items will be assessed at consultations C1 and Cf:

- CGI in the middle and at the end of treatment [[[15]](#endnote-15)];
- Psychometric improvement, as assessed by psychologists using a VAS;
- Tolerance, with particular emphasis on neurological tolerance.

## paraclinical examinations

These examinations will be carried out at all consultations, at six-month intervals: determination of blood formula, iron and ferritin concentrations and thyroid assessment. Photocopies of the results will be rendered anonymous and included in the observation notebook.

## missing data

If a patient does not return for examination after a year of treatment, the data for the intermediate examination will also be treated as those of the final examination. If no data are collected after the initial examination, these data will be considered missing for the analysis. Reasons for leaving the trial early will systematically be sought, via telephone interviews at least, to check that there is no link between withdrawal from the trial and the treatment (particularly as concerns tolerance).

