## trial description and chronology

The total duration of follow-up for any given patient in the trial will be 1 year ± 30 days.

The first medical consultation will include:

- Information about the trial and the signing of the consent form;
- Confirmation of the diagnosis, checking for the presence of karyotyping data in the patient's medical records;
- Checking the inclusion and non-inclusion criteria, including, in particular, ability to undergo the revised Brunet-Lezine test for determining developmental age (DA);
- A general clinical and neurological examination, with measurement of height, weight and CC;
- Prescription of routine biological tests (blood formula, iron, ferritin, thyroid assessment) and other specific examinations, if necessary.

The first consultation with the psychologist will include a psychological examination and the revised Brunet-Lezine test.

Intermediate contact will be made with the parents at intervals of no more than two months. During these intermediate contacts by telephone, the interview by a doctor from the CMJL will focus particularly on the tolerance of folinic acid treatment.

If necessary, the final consultation may take place early, in cases of withdrawal from the study.

The intermediate consultation (6 months ± 15 days) and the final visit (1 year ± 30 days) will include:

- A general clinical and neurological examination, with measurement of height, weight and CC;

- The recording of any adverse events;

- The recording of the doctor's opinion concerning the child (CGI);

- The recording of the overall opinion of the psychologist concerning the development and behaviour of the child on a visual analogue scale (VAS);

- The revised Brunet-Lezine test (determination of DA);

- The recording of the parents' opinion on the treatment of the child;

- The prescription of routine biological tests (blood formula, iron, ferritin, thyroid assessment) and other specific examinations if required.

The entire study will therefore include only standard examinations: three medical examinations, three psychological examinations and three sets of standard biological tests. Between consultations, three to five telephone contacts are planned to help the family and for the monitoring of tolerance and compliance with treatment. If possible, all the examinations will take place on the same day, with the same doctor and the same psychologist.

The total duration of the inclusion period will be 1.5 years.

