### Efficacy

Efficacy will be evaluated using several criteria.

The principal evaluation criterion will be the change in developmental age, the profile of which is known for patients with Down's syndrome [[[16]](#endnote-16)]:

Translation for the figure: Age mental = mental age; Age reel = real age.

Developmental age will be assessed by the revised Brunet-Lezine test administered before (DA0) and after (DAf) treatment: (DAf - DA0). The revised Brunet-Lezine test is widely recognised as a test for the evaluation of psychomotor development in infants. It has been validated and its metrological qualities (sensitivity, fidelity-homogeneity, dispersion and validity, including for Down's syndrome children) are well known. For further information about this test, please consult reference 13.

The other criteria for efficacy evaluation will be:

- CGI, as recorded by the doctor;
- A score for psychologist satisfaction, estimated on a VAS, evaluating the opinion of the psychologist on the subjective improvement of the child since the start of treatment.
- The response of the parents to the question "If possible, would you like to continue this treatment ?" The response will be scored as follows: in favour of continuing treatment/against continuing treatment/does not know or no opinion expressed.

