## number of cases

The number of subjects required has been determined with nQuery Advisor® software. Calculations have been carried out for developmental quotient, based on previous data and the following assumptions for calculation of the number of subjects per group:

Two-tailed Student's t tests with equal numbers in the two groups

 risk 0.05

Mean improvement on placebo over one year 0.666 years

Mean improvement on folinic acid over one year 0.900 years

Standard deviation 0.4 years

Power (1-) 80%

Two-group t test (identical numbers of subjects each group); power (puissance); number of subjects per group

If we adopt a power of 80%, as is usual for phase II-III studies, we require 47 subjects per group (94 in total). We have therefore decided to recruit 50 subjects per group, giving 100 complete observations in total.

An intermediate statistical analysis will be carried out without decoding for the first 60 subjects, to check that the variances of the two groups are equal. The number of subjects required will be recalculated at this point. If the number of subjects must be changed, an amendment to the protocol will be required.

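### Entering the 6-month developmental age as the final value under-credits carried-forward children and biases the primary comparison when carry-forward differs between arms

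*Protocol*

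**What the plan says.** The Missing data section of the protocol covers two situations. If a child does not come back at one year, "the data for the intermediate examination will also be treated as those of the final examination". If nothing was recorded after baseline, a different rule holds: "If no data are collected after the initial examination, these data will be considered missing for the analysis". Carry-forward therefore applies only to children who have a 6-month examination.

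The Efficacy section defines the primary criterion as an unscaled difference: "administered before (DA0) and after (DAf) treatment: (DAf - DA0". The Tests used section applies a t test (or ANOVA) to this change and states no adjustment for elapsed time.

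The trial description sets the timing: "The intermediate consultation (6 months ± 15 days) and the final visit (1 year ± 30 days) will include". The Number of cases section gives the expected gains: "Mean improvement on placebo over one year 0.666 years", "Mean improvement on folinic acid over one year 0.900 years" and "Standard deviation 0.4 years".

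Two further provisions matter. The trial description lets the final consultation be brought forward when a child withdraws. The Exclusion criteria section asks for the final examination within a month of withdrawal.

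**The concern.** The outcome is growth, and the protocol itself expects it to accumulate over the year. A 6-month DA entered as the final DA makes DAf - DA0 a half-year gain, yet it is analysed alongside full-year gains as if it were one.

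The resulting error differs by arm if the share of carried-forward children does. The section on losses to follow-up lists withdrawal reasons that could depend on treatment, such as an adverse effect of the product, clear aggravation or poor compliance. The Missing data section asks for a check that withdrawal is unrelated to treatment, but offers no other analysis if it is related. At stake are the type I error and the power of the primary test, and the size of the reported effect.

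**Working it through.** **Inputs from the protocol (Number of cases).** Gains over one year m = 0.666 (placebo) and 0.900 (folinic acid), difference 0.234; SD 0.4; two-sided alpha 0.05; 50 per group. The section labels the calculation as one for developmental quotient, but the inputs are gains in years, so they are read here as DA gains.

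**The plan's own figure.** The noncentral t calculation gives 46.85, rounded up to 47 per group, as stated. Power is 80.1% at 47 and 82.5% at 50 per group.

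**Assumptions not in the protocol.**
- f, the share of the one-year gain reached at 6 months, is 0.5 (linear growth), with a range of 0.4 to 0.6. The protocol's growth figure is not available to check this.
- The variance of the gain is proportional to f.
- Being carried forward is unrelated to the child's own outcome.
- The proportion carried forward, p, is illustrative.

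**Formulas.**
- Arm mean: m × (1 - (1 - f)p), which is m × (1 - p/2) at f = 0.5.
- Arm variance at f = 0.5: (1 - p) × 0.16 + p × 0.08 + p(1 - p)(m/2)².
- Rejection rate: noncentral t with 98 degrees of freedom, SE = √[(sum of the two variances)/50].

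**Credit per carried-forward child at f = 0.5.** Placebo 0.666/2 = 0.333 years; folinic acid 0.900/2 = 0.450 years.

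**No true effect (m = 0.666 in both arms).** The bias is 0.333 × (difference in carry-forward proportions), against the arm with more carry-forward.

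| Carried forward | Bias (years) | Type I error |
|---|---|---|
| 4% vs 2% | 0.333 × 0.02 = 0.007 | 5.1% |
| 10% vs 5% | 0.333 × 0.05 = 0.017 | 5.5% |
| 15% vs 5% | 0.333 × 0.10 = 0.033 | 7.0% |
| 20% vs 5% | 0.333 × 0.15 = 0.050 | 9.4% |

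For 20% vs 5% in full: the variances are 0.1617 and 0.1613, SE = 0.0804, and 0.050/0.0804 = 0.62. As f goes from 0.6 to 0.4, the bias for 15% vs 5% runs from 0.027 to 0.040 years.

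**Design effect (true difference 0.234).**

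| Active / placebo | Expected difference | Power |
|---|---|---|
| 10% / 10% | 0.900 × 0.95 - 0.666 × 0.95 = 0.222 | 77% |
| 20% / 5% | 0.900 × 0.90 - 0.666 × 0.975 = 0.161 (-31%) | 49% |
| 5% / 15% | 0.900 × 0.975 - 0.666 × 0.925 = 0.261 (+12%) | 89% |

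The two arms' errors cancel only when 0.333 × p(placebo) = 0.450 × p(active), that is, when placebo carry-forward is 0.900/0.666 = 1.35 times active carry-forward.

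**Fair comparator.** Children without a 12-month value cost power under any analysis, so carry-forward should be set against 12-month completers only, which is unbiased under the assumptions above. With 10% lost in each arm (45 per arm), completers-only power is 78.4%. With 20% / 5% lost (40 and on average 47.5), it is about 77%.

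**The case against.** The strongest defence is that the rule may seldom be used. It needs a child who was seen at 6 months and has no later examination. Withdrawals are to have a final examination within a month, and losses before 6 months are treated as missing. For irritability, the dosing section provides for dose reduction and, if possible, re-evaluation before treatment is stopped, so such a child is among the less likely to be carried forward. With 4% against 2% carried forward, the effect on type I error is negligible.

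This limits the size but leaves the rule defective. An early final examination also covers less than a year of growth, and no adjustment for time is stated. Nor does the protocol say whether an early final value or the 6-month value is used for a child who has both but is not seen at one year.

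A reader might infer four stronger things that the documents do not support:
- That the primary result is wrong by construction. The bias depends on how many children are carried forward and how unequally. With equal proportions and no drug effect it is zero.
- That every dropout is scored at 6 months. The provisions above rule this out.
- That DA rises steadily in every child. The protocol gives only group means and an SD.
- That the rule alone lowers power from 82.5% to 77% at 10% carry-forward in both arms. Of that fall of about 5.5 points, only about 1.3 is due to the rule (78.4% to 77%, before rounding); the rest is lost data.

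**Conclusion.** The concern stands in a conditional form. The rule treats a part-year gain as a full-year gain on an outcome that the protocol expects to grow, and it works against the arm with more carried-forward children. Equal carry-forward shrinks a true difference only slightly (0.234 to 0.222 at 10%).

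The serious harm comes from imbalance. At 20% against 5%, type I error is 9.4% with no drug effect. Under the design effect with the larger share on active, power is 49%, where completers only would have about 77%. The opposite imbalance, 5% active and 15% placebo, inflates the difference to 0.261.

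These sizes rest on assumed carry-forward rates, on about half the gain being reached by 6 months, and on carry-forward being unrelated to outcome. The direction of the bias needs only further growth after 6 months. How much it matters depends on how many children are carried forward and how unequally. The rule should still be changed, because it sits in the primary comparison and is cheap to replace.

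**What to change.** Remove carry-forward from the primary analysis. Before decoding, specify a repeated-measures mixed model of all observed DA values with treatment, visit, treatment-by-visit, baseline DA and age, and make the 12-month treatment difference primary. The 6-month value then informs the 12-month estimate without standing in for it. Other valid likelihood-based or multiple-imputation methods would also serve.

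State how early final examinations enter: at their actual time (time as a continuous variable) or under a stated visit window, and not as 12-month values. Without this, the short-follow-up problem remains. Keep carry-forward at most as a labelled sensitivity analysis.

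Cost: wording in the Missing data and Tests used sections and slightly more analysis work. The DA tests at 0, 6 and 12 months are already scheduled and SAS is already allowed, so no further data are needed. The downside is a missing-at-random assumption, which should be stated.

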## evaluation criteria

### Tolerance of folinic acid

All adverse events will be recorded, whether or not they appear to be related to the treatment. Clinical and biological tolerance will be evaluated:

- Clinical tolerance will be assessed on a case-by-case basis, with dose adjustment if required.
- Biological tolerance will be assessed by monitoring changes in biological variables. Case-by-case follow-up will be carried out, using the results of the first laboratory tests after the initiation of folinic acid treatment as reference. These data will also be used to assess the significance of changes in biological test data for all the patients treated.

### Efficacy

Efficacy will be evaluated using several criteria.

The principal evaluation criterion will be the change in developmental age, the profile of which is known for patients with Down's syndrome [[[16]](#endnote-16)]:

Translation for the figure: Age mental = mental age; Age reel = real age.

Developmental age will be assessed by the revised Brunet-Lezine test administered before (DA0) and after (DAf) treatment: (DAf - DA0). The revised Brunet-Lezine test is widely recognised as a test for the evaluation of psychomotor development in infants. It has been validated and its metrological qualities (sensitivity, fidelity-homogeneity, dispersion and validity, including for Down's syndrome children) are well known. For further information about this test, please consult reference 13.

The other criteria for efficacy evaluation will be:

- CGI, as recorded by the doctor;
- A score for psychologist satisfaction, estimated on a VAS, evaluating the opinion of the psychologist on the subjective improvement of the child since the start of treatment.
- The response of the parents to the question "If possible, would you like to continue this treatment ?" The response will be scored as follows: in favour of continuing treatment/against continuing treatment/does not know or no opinion expressed.

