## exclusion criteria

Patients will be removed from the study if one of the following criteria is met:

- Occurrence of myeloproliferative syndrome;
- Initiation of thyroid hormone treatment during the study (patients already on stable thyroid extract treatment for more than 3 months may be included);
- Folic or folinic acid treatment (other than that studied) for more than two months during the trial: Alvityl®, Azedavit®, Azinc®, Carencyl®, Cernevit®, Elevit®, Elvorine®, Folinate de calcium, Folinoral®, Forvital®, Léderfoline®, Lofenalac®, Osfolate®, Perfolate®, Plenyl®, Quotivit®, Soluvit®, Spéciafoldine®, Synergyl®, Tardyféron®, Vivamyne®, Zédène®,
- Treatment with a drug with antifolate activity for more than two months of the year (methotrexate, phenytoin).

For patients withdrawing early from the trial, as much information as possible will be obtained by telephone and the final examination will be carried out as soon as possible (within a month of withdrawal).

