# losses to follow-up and premature withdrawal from the trial

The reasons for which a subject may be withdrawn from the trial are as follows:

- Demand from the patient, withdrawal of consent;
- Clear aggravation;
- Occurrence of a serious or unpleasant adverse effect associated with the product tested;
- Poor compliance
- Occurrence of myeloproliferative syndrome;
- Initiation of thyroid hormone treatment during the trial (patients already on thyroid extracts treatment for more than 3 months may be included);
- Treatment with folic or folinic acid (other than the product studied) for more than two months during the trial.

The reasons for the treatment being stopped early or for premature withdrawal from the trial should be documented and reported clearly in the observation notebook, on the appropriate page. All cases of premature cessation of treatment or withdrawal will be analysed in terms of tolerance and efficacy, provided that it is possible to obtain the appropriate data.

The number of subjects lost to follow-up should be minimised and as much information as possible should be collected for these subjects (by postal or telephone contact, for example).

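### The 6-month carry-forward also covers the parents' answer on continuing treatment, so a family that withdraws and misses the early final examination can be counted in favour at one year

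*Protocol*

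**What the plan says.** The protocol summary lists the parents' opinion on continuing treatment among the secondary criteria, and the section on efficacy makes it one of the efficacy criteria, scored in three categories: "in favour of continuing treatment/against continuing treatment/does not know or no opinion expressed". The schedule table and the section on trial description and chronology place it at both the intermediate and the final visit ("The recording of the parents' opinion on the treatment of the child").

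The section on missing data sets the rule for a missing final visit: "If a patient does not return for examination after a year of treatment", then "the data for the intermediate examination will also be treated as those of the final examination". No variable is exempted. The same section adds: "Reasons for leaving the trial early will systematically be sought, via telephone interviews at least".

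Three other places bear on families who leave:

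- Trial description and chronology: "If necessary, the final consultation may take place early, in cases of withdrawal from the study".
- Exclusion criteria: for early withdrawals, information is gathered by telephone and "the final examination will be carried out as soon as possible (within a month of withdrawal").
- Losses to follow-up and premature withdrawal: the listed reasons include "Demand from the patient, withdrawal of consent" and a serious or unpleasant effect of the product. Withdrawals are analysed for tolerance and efficacy as far as data can be obtained.

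**The concern.** Carrying forward a developmental age keeps a value that is out of date. Carrying forward a stated wish to continue treatment can keep a value at odds with what the family did next. A family that is content at month 6 and stops at month 8 because the child tolerates the product badly has changed its view, and the trial may hold that reason in its own records. Under the rule as written, the month-6 answer would still be the one analysed at one year.

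The item is meant to show whether parents find the treatment acceptable and useful. If such families are more frequent in one arm, that arm's in-favour proportion is raised by its own withdrawals, and the comparison is distorted towards the less well accepted arm.

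**Working it through.** **Step 1. Does the rule reach this item?** The rule concerns the data of the intermediate examination as a whole. The parents' answer is collected at that examination. No exception is stated, so it is covered.

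**Step 2. Which families are affected?**

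| Course of the family | Answer used at one year |
| --- | --- |
| Seen at 12 months | Its own 12-month answer |
| Leaves after month 6, seen at an early final examination | Natural reading: the answer given there. Literal reading: the 6-month answer, because the child has not returned after a year of treatment |
| Leaves after month 6, not seen again | The 6-month answer. The telephone interview records the reason for leaving, but nothing says it changes the score |
| No data after the initial examination | Missing |

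The third row is affected on any reading. The second is affected only because no section states which source takes precedence.

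**Step 3. Size.** The plan gives no figure for this item. The denominator is the 50 per arm in the section on number of cases. The sample size behind it reproduces: a difference of 0.900 - 0.666 = 0.234 years, SD 0.4, two-sided 0.05 and 80% power give 46.85 by the t test, rounded up to 47. The present point does not depend on that calculation.

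Each affected family shifts the in-favour proportion by 1/50 = 2 percentage points.

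The protocol states no dropout rate, so the number of families is an assumption. Let w be the withdrawals after month 6 per arm, e the share with no early final examination, and q the share in favour at month 6.

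Affected families = w × e × q; shift in points = 100 × w × e × q / 50.

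| w | e | q = 0.5: families (points) | q = 0.8: families (points) |
| --- | --- | --- | --- |
| 2 | 0.5 | 0.5 (1.0) | 0.8 (1.6) |
| 2 | 1 | 1.0 (2.0) | 1.6 (3.2) |
| 5 | 0.5 | 1.25 (2.5) | 2.0 (4.0) |
| 5 | 1 | 2.5 (5.0) | 4.0 (8.0) |
| 10 | 0.5 | 2.5 (5.0) | 4.0 (8.0) |
| 10 | 1 | 5.0 (10.0) | 8.0 (16.0) |

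With e = 0 and the natural reading of the rule, every entry is zero. The range is therefore 0 to 8 families, or 0 to 16 points, per arm. Under the literal reading, early examinations do not help and the e = 1 rows apply.

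**Step 4. Comparison between arms.** The error in the difference is (affected families on folinic acid - affected families on placebo) / 50. Equal numbers cancel; unequal numbers favour the arm with more. The protocol gives no basis for saying which arm that would be.

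**The case against.** The strongest reply is that the protocol already plans for these families. The exclusion criteria section schedules a final examination within a month of withdrawal, and the parents' opinion is among the final-visit items. A family leaving at month 8 is due to be asked again by about month 9, and the carry-forward then reads naturally as a fallback for children not seen at all. This stands, and it limits the problem. It does not remove it: the trial description only permits an early visit, the losses section accepts that data may be unobtainable, and families who have withdrawn consent are plausible candidates to miss another visit.

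A reader might infer that every family leaving after month 6 is scored on its 6-month answer. The planned early examination rules that out as the normal outcome.

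A reader might also infer that withdrawal always contradicts an earlier favourable answer. It does not. A family can leave because of the visits, the blood tests or the blinding and still want the treatment, and some listed reasons, such as starting thyroid hormone, say nothing about parental opinion. For the same reason, scoring all family-request withdrawals as against would impute an answer never given.

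A large gain for folinic acid is not supported either. The only tolerance figure in the document is one case of excitation among 69 patients in an open study with a wider age range: 1/69 = 1.4%, or 50 × 1/69 = 0.7 per arm. That argues for a small number of intolerance withdrawals, though it says nothing about families leaving for other reasons.

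Finally, reasons for leaving are documented and analysed, so the negative verdict is not lost from the trial. It is lost only from this endpoint. An analysis plan could handle the item differently, but the protocol states a rule, and as written the rule covers it.

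**Conclusion.** The point holds in a limited form. The carry-forward can score a withdrawn family as in favour of continuing when that family gave no later answer, and the wording leaves open whether it also overrides an answer given at an early final examination. Each such family moves the arm's in-favour proportion by 2 points. The total depends on assumed counts, since the protocol supplies none, and may be nil if early final examinations are achieved and take precedence. The direction of any bias between arms cannot be determined from the document. The item is secondary, and the principal criterion is not affected through it. It is worth correcting because a stated rule can give a wrong value and the correction is nearly free.

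**What to change.** In the section on missing data:

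1. State that data from an early final examination take precedence over carried-forward 6-month data, which reconciles this section with the trial description and the exclusion criteria.
2. Exempt the parents' opinion from carry-forward.
3. Add the continuation question to the telephone interview already planned for families who leave, and use that answer as final where there was no early examination.
4. Where no answer is obtained, score the existing category for not knowing or expressing no opinion, and report reasons for withdrawal by arm beside the result. Scoring such families as against belongs in a sensitivity analysis only.

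The cost is a few lines of text, one telephone question and a few more no-opinion scores, which slightly reduce the number of informative answers.
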